### Primary outcome

The primary outcome will be the laboratory confirmed number of CA-BSIs per 1000 line-days, following the CDC definition: (1) one or more positive blood culture(s) (not skin flora) and no other infection source; or (2) one positive blood culture and clinical signs and no other infection source [28]. The diagnosis will be made jointly by a member of the research team (OH, [name]) and an infection control practitioner. Discrepancies between these persons will be resolved through discussion until consensus is reached; or will be solved by an independent physician using the institutional microbiological database and the patient file. The CDC defines CA-BSI as a primary BSI if a CVC was in place 48 hours before the development of the BSI and if it is not bloodstream related to an infection at another site [29]. A CVC in situ is defined as a catheter introduced into a vein that terminates close to the heart or into one of the great vessels, and which is used for infusion, blood sampling or hemodynamic monitoring. Data concerning the number of line-days will be abstracted from the digital patient data management systems. It may be an umbilical venous catheter, a percutaneous CVC, a tunneled catheter, a port, or a peripherally inserted central catheter (PICC) [30].

### Secondary outcomes

Rate of adherence to the CVC insertion bundle and rate of adherence to the maintenance bundle will serve as secondary outcomes.

The attending nurse will assess adherence to the CVC insertion bundle during the insertion procedure (Table 3). To this aim we designed a digital tab with drop-down menu for the two different patient data management systems. The time out procedure prior to the CVC insertion is predominantly added for creating safety awareness during insertion (Additional file 1: Table S1). During the insertion procedure all involved healthcare workers are encouraged to make comments and to stop the procedure in case of violation of insertion bundle. Intravenous medication preparation and administration items will serve to measure adherence to the CVC maintenance bundle (Table 4). Purpose-trained nurses will randomly assess these items during planned daily care.

### Economic costs and benefits

Additionally, the cost-effectiveness of the implementation of the CVC bundle will serve as a secondary outcome measure, to be established through cost-effectiveness analysis. Taking a health care perspective, the cost-effectiveness analysis will make a comparison between the pre-intervention period ('usual care’) and the post-intervention period regarding both the total costs and the number of CA-BSIs per 1,000 line-days.

Among the costs included will be the direct medical costs relating to CA-BSIs. These costs will be calculated by multiplying resource utilization with a unit cost price. As much as possible, real economic cost prices will be used rather than charges. Cost prices will be calculated according to established methods [31]. The time horizon will be from the patient’s hospital admission until discharge.

Any possible savings on the costs of medical care need to be balanced against the costs of implementing the CVC bundle. All costs related to the implementation process will be taken into account. This implies that the study will take account of the costs for the implementation strategies (Table 5), as well as the changes in the care implicit to the implementation of the CVC bundle (Table 2) insofar as they result in additional costs compared to usual care. To arrive at total costs, we will include both personnel costs, material costs, and overhead costs.

### Data collection

Four nurses trained in observation will unobtrusively observe staff when they apply the insertion and maintenance bundles. Observation will be guided by a self-designed structured case report form. The staff will be unaware of the reason for the observations; they are already frequently observed for training or research purposes. Data collection will be at random moments seven days a week and 24 hours a day. Sealed envelopes will be used to ensure an equal allocation of these two-hour observations over the wards and observation times during the day. Data on sex, (birth) weight, and age of the patients involved will be retrieved from the patient data management systems (Additional file 3: Table S2). Disease severity of infants admitted to the neonatal intensive care unit will be documented by the Clinical risk index for babies (CRIB) score [32]; that of children admitted to the pediatric intensive care unit by the Pediatric Risk of Mortality III score (PRISM III) [33] or Pediatric Index of Mortality (PIM) score [34]; that of children admitted to the oncology department by the Lansky score (children ≤ 9 year) [35] or Karnofsky score (children > 10 year) [35]. There is no suitable disease severity score for patients admitted to the medium care ward, due to the diversity of diseases.

### Statistical analysis

Data will be expressed as median and interquartile range (IQR), unless indicated otherwise. The baseline data showed that 69 children developed a CA-BSI. The effect of the intervention on rate reduction will be determined with a segmented loglinear regression analysis of interrupted time series, using a pre-intervention, intervention, and post-intervention segment. The slope or trend of the segments indicates the rate of change in time. An abrupt change at the time of the implementation indicates an immediate effect. Introducing slopes (percentual changes in time in infection rate before and after the implementation) corrects for unassociated background trends. A change in slope after the introduction of the intervention may identify a gradual effect of the implementation [17,36]. We aggregated CA-BSIs per 1,000 line-days over 3-month periods. This figure will also be used in the cost-effectiveness analysis, which is concerned with the differences in outcome and total costs between the pre-intervention and the post-intervention period. Cost-effectiveness is assessed through the calculation of an incremental cost-effectiveness ratio (ICER). The ICER is calculated as the incremental costs per case of CA-BSI per 1,000 line-days avoided. The cost-effectiveness analysis will include a sensitivity analysis to assess how sensitive the results are to any assumptions made.

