#### ***Measuring***

The outcome measure is the number of CA-BSIs per 1000 line-days, calculated by dividing the number of bloodstream infections by the risk-adjusted denominator 1000 line-days. As a baseline measurement we prospectively collected data from 1st January 2011 to 1st January 2012. Over that period the number of CA-BSIs per 1000 line-days was 11.2 at the neonatal intensive care unit and 7.9 at the pediatric intensive care unit.

As secondary outcome (process measures) we selected degree of adherence to safety procedures, e.g. maximum sterile barrier during the CVC insertion procedure and adherence to hygienic protocols during intravenous administration. Adherence will be documented with the use of two observation tools (Tables 3 and 4). Performance related to the insertion procedure will be measured with two tools: use of the time out procedure that is linked with the CVC insertion protocol (Additional file 1: Table S1) and a questionnaire daily popping up in the patient’s electronic record informing after signs of infection at insertion site as well as the need of having the CVC in place.

**Table 3 T3:** Process indicators CVC insertion monitoring form

	**Process indicator**	**Satisfied**
1	Skin cleaned with alcohol 70% with chlorhexidine 0.2%; or chlorhexidine 0.2% in water in infants with a gestational age < 26 weeks	Yes O No O
2	Air dry of at least 30 seconds after skin preparation prior to guide-wire insertion	Yes O No O
3	New needle used after each attempt to insert a CVC through the intact skin	Yes O No O
4	Sterile drape covering the patient for least 80%	Yes O No O
5	The provider inserting the CVC used maximum sterile barrier e.g. sterile gown, double sterile gloves, mask, and hat	Yes O No O
6	Optimal insertion site was selected or another site was argued for	Yes O No O
7	Echo use during insertion of jugularis and subclavia catheter	Yes O No O
8	Chlorhexidine impregnated sponge used in infants < 40 weeks gestational age	Yes O No O

*CVC* central venous catheter.

**Table 4 T4:** Process indicators CVC nursing care monitoring form

	**Process indicator**	**Satisfied**
1	Appropriate hand hygiene prior to preparation of intravenous medication	Yes O No O
2	Disinfection of the cap or ampoule’s surface using alcohol 70%	Yes O No O
3	Applying 30 seconds air drying time after disinfection ampoule’s surface	Yes O No O
4	Disinfection of connector with alcohol 70%^#^	Yes O No O

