The Pronovost-model is merely medical oriented. The main point of departure from the model is knowledge transfer, which fits into physicians’ learning style [44]. Goossens et al. found that strong scientific evidence was the strongest determinant of physicians’ behaviour [44]. However, regarding our goal, a clear healthcare team angle seems to be more appropriate for a broad dissimilation of improved hygienic behaviour among all members of the multidisciplinary team. Nurses have a more active learning style, and the strongest determinant of knowledge acquisition was found the be the fact whether the subject was 'interesting […] or not’ [44]. This phenomenon affects whether a new procedure is potentially beneficial for patients or gets embedded in the daily care.

We postulate that the proposed study has methodological strength because it is guided by a validated implementation model that has been translated into a hands-on program and is described in detail for implementation hospital-wide. Furthermore, regularly reporting the outcomes is in line with the ORION statement promoting transparent reporting on intervention studies aimed to reduce nosocomial infections. ORION recommended interrupted time series as preferable method for analysis showing the change in results over time.

We anticipate several challenges in this study. (1) Effectiveness of interventions is preferably evaluated by randomisation into an intervention and control group. However, this method is inappropriate for our aim to implement an intervention hospital-wide, and the interrupted time series design is the second best solution and in line with the ORION guidelines (2). The CVC bundle is adapted and tailor made for our hospital. Although this results in less generalizability, this naturalistic approach could help develop practical implementation strategies for other hospitals or other interventions. (3) The effective ingredients of the bundle are still unclear. However, as some interventions have been shown to be effective it would be unethical to test all separate interventions. (4) To control for confounders is a challenge due to the different safety climates in the different departments. By establishing a clear leadership we will try to show the benefits of a univocal approach towards infants’ CVC care.

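### The primary model as described adjusts hospital-wide quarterly infection rates only for time trends, so a shift in line-days between wards at implementation can distort the level change and the cost-effectiveness comparison

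*Protocol article*

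**What the plan says.** - **Outcome.** The Measuring section describes the rate as "calculated by dividing the number of bloodstream infections by the risk-adjusted denominator 1000 line-days". It reports that in 2011 "the number of CA-BSIs per 1000 line-days was 11.2 at the neonatal intensive care unit and 7.9 at the pediatric intensive care unit". No baseline rate is given for the medium care units, which also take part (Setting and participants).
- **Model.** The Statistical analysis section plans a "segmented loglinear regression analysis of interrupted time series, using a pre-intervention, intervention, and post-intervention segment". On the data that enter it, the section says: "We aggregated CA-BSIs per 1,000 line-days over 3-month periods". The only adjustment named is the inclusion of slopes, which "corrects for unassociated background trends".
- **Scope.** Objective 1, at the end of the Background, concerns the effect of hospital-wide implementation on incidence over 48 months. Ward-level findings appear only under Evaluate, as quarterly feedback to ward management.
- **Cost-effectiveness.** The same quarterly figure feeds a comparison of the pre-intervention with the post-intervention period. No trend or case-mix correction is stated for that comparison.
- **Confounding.** The Discussion concedes: "To control for confounders is a challenge due to the different safety climates in the different departments". The remedy it names is clear leadership, which is not an analysis step.

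**The concern.** Line-days are an exposure denominator. They make a quarter with more catheter time comparable with one that has less, but a line-day in the neonatal unit counts the same as one in medium care. The article's own figures show a crude rate ratio of 1.42 between its two intensive care units, and the Background links high neonatal rates to immature host defence. Calling the denominator risk-adjusted suggests that this has been dealt with, and it has not.

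There is no control group. If the distribution of line-days over wards changes when the bundle is introduced, the overall rate changes even if no ward's rate does. Such a change is plausible, because the bundle includes a daily question on whether the catheter is still needed, and this may shorten catheter use more in some wards than in others. The distortion can go either way. If lines are removed mainly in low-rate wards, the overall rate rises although no ward has become less safe.

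The severity scores listed under Data collection cannot easily serve as a common adjuster. They are on different scales in different units, and the section says that none suits medium care. Ward is the obvious case-mix variable that could be used throughout.

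**Working it through.** **1. The plan's own power figure.** The Sample size section gives 141 cases before the intervention, equal periods before and after, a rate ratio of 0.70 and 80% power. Two-sided alpha 0.05 is assumed here, because the section states an alpha only for the adherence outcomes.

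- Expected cases after: 0.70 × 141 = 98.7.
- SE of the log rate ratio: √(1/141 + 1/98.7) = 0.131.
- Power: Φ(0.357/0.131 − 1.96) = 77.6%.

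A pooled-null variance gives 78.5%, a simulated likelihood-ratio test 78.3% and the Schoenfeld formula 78.8%. The stated 80% is reproduced to within about two points, so there is little power to spare.

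**2. Mix effect from the two documented rates.** Let s be the neonatal share of line-days in the two intensive care units. Then pooled rate = 11.2s + 7.9(1 − s), with both unit rates held constant. The shares are not in the article and are assumed.

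| Neonatal share, before → after | Pooled rate | Ratio |
|---|---|---|
| 50% → 40% | 9.55 → 9.22 | 0.965 |
| 50% → 60% | 9.55 → 9.88 | 1.035 |
| 60% → 40% | 9.88 → 9.22 | 0.933 |
| 40% → 60% | 9.22 → 9.88 | 1.072 |
| 100% → 0% (extreme) | 11.2 → 7.9 | 0.705 |

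Shifts of 10 to 20 points therefore move the pooled rate by about 3 to 7%.

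**3. What this does to the simple pre/post comparison** (141 cases before).

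- No bundle effect, mix ratio k = 0.933: SE = √(1/141 + 1/131.6) = 0.121 and −ln(0.933)/SE = 0.57. The two-sided rejection rate is Φ(0.57 − 1.96) + Φ(−0.57 − 1.96), about 9% instead of 5%.
- True ratio 0.70 with an adverse mix ratio of 1.07: the observed ratio is 0.749, SE = √(1/141 + 1/105.6) = 0.129, and power = Φ(0.289/0.129 − 1.96), about 61% instead of about 78%.

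These two results belong to the simplified comparison. In the segmented model the level change is estimated less precisely, so its rejection rate would move less. An abrupt mix shift at implementation would still bias the estimate.

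**4. Shifts to or from other wards.** Here both the shares and the other-ward rate are assumptions. The intensive care rate is set at the midpoint, (11.2 + 7.9)/2 = 9.55, and the other-ward rate is varied from 1 to 6 per 1000 line-days.

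| Other-ward share, before → after | Ratio at rate 1 | at 2 | at 4 | at 6 |
|---|---|---|---|---|
| 30% → 40% | 0.88 | 0.90 | 0.93 | 0.96 |
| 30% → 50% | 0.76 | 0.79 | 0.86 | 0.92 |
| 30% → 20% | 1.12 | 1.10 | 1.07 | 1.04 |

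Setting and participants gives medium care 29,436 of 53,541 − 5,588 = 47,953 participating patient-days, or 61%. These are patient-days, and the article gives no way to convert them to line-days.

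**5. How firm the 1.42 is.** The article reports: "The baseline data showed that 69 children developed a CA-BSI". If all 69 came from the two intensive care units and split 35 to 34 (an assumption), the 95% interval for 11.2/7.9 is 1.42 × exp(±1.96 × √(1/35 + 1/34)), or 0.88 to 2.27.

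**The case against.** **Pooling over wards is not stated.** The aggregation sentence is about calendar time, and a ward term could sit in a fuller plan that is not shown. This is right as far as it goes. The single series is inferred from the hospital-wide objective, a model description that names only segments and slopes, a power calculation on one overall case count, and a single figure carried into the cost-effectiveness analysis. What does not depend on the inference is the wrong label on the denominator and the non-analytic answer to a confounding problem that the article itself raises.

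**The slopes already adjust.** They largely absorb a steady drift in mix. They do not absorb a shift that coincides with implementation, and no slope correction is stated for the cost-effectiveness comparison.

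**A mix change caused by the daily catheter-need question is a consequence of the bundle, and the hospital-wide rate is a legitimate target.** Both statements are fair. But the hypothesis is that the bundle reduces infections, and a rate that moves only because line-days have moved between wards does not show this in either direction.

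**Stronger readings that the article does not support.** A reader might infer that a mix shift could mimic the whole planned effect. Even a complete move from the neonatal to the pediatric unit gives only 0.705, and the larger figures in step 4 rest on assumed rates and shares. A reader might also infer that pooling wards with different rates makes Poisson intervals too narrow. It does not: independent Poisson counts with different rates sum to a Poisson count. Moreover, the Poisson error distribution is named only in the Sample size section, under declared simplifying assumptions, and the Statistical analysis section fixes no variance.

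**Conclusion.** The point holds in a limited form. As described, the primary model has no protection against a change in line-day mix that coincides with implementation, and the term risk-adjusted is wrong for a denominator that adjusts only for exposure time. On the two documented rates and assumed shares, the likely distortion is about 3 to 7% in either direction. That is well short of the planned 30% drop, but it matters in a design with roughly 78 to 79% power. Shifts involving lower-rate wards could distort more, but the article gives neither those rates nor any line-day shares. The conclusion assumes that the analysis is a single hospital-wide series, which is the natural reading but not an explicit statement. The difference between the two unit rates is itself imprecise.

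**What to change.** 1. Fit the segmented loglinear model to ward-by-quarter infection counts, with log line-days as offset and ward group (neonatal intensive care, pediatric intensive care, medium care) as a fixed factor. Alternatively, standardise each quarter's rate to the baseline line-day shares. Either keeps the hospital-wide objective.
2. Estimate the dispersion (quasi-Poisson or negative binomial) rather than carry over the Poisson assumption of the power calculation.
3. Use the ward-standardised rate in the cost-effectiveness comparison.
4. Delete the term risk-adjusted from the outcome description in Measuring.
5. Report ward-specific rates beside the overall effect, since a common ward-adjusted effect assumes the same proportional change in each ward group.

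The cost is small. Three ward groups add two parameters. Ward-level findings are already to be reported each quarter, and line-days come from the electronic patient data systems. If the 69 baseline cases cover all three groups, cells average 69/(3 × 4), or about 6 cases, which a count model can handle. The one new item is a rule for attributing infections and line-days when a child moves between wards, fixed before the post-intervention data are examined.

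### As worded, the ICER sets a total-cost difference with no stated denominator against a rate difference per 1,000 line-days, using a pre/post contrast without the trend correction applied to the effect estimate

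*Protocol article*

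**What the plan says.** The protocol article describes the economic analysis in two places.

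- **Economic costs and benefits.** The two periods are compared "regarding both the total costs and the number of CA-BSIs per 1,000 line-days". The cost total is described by its components: "To arrive at total costs, we will include both personnel costs, material costs, and overhead costs". It includes all costs of the implementation strategies in Table 5 and any extra cost of care under the bundle. "The time horizon will be from the patient’s hospital admission until discharge".
- **Statistical analysis.** "We aggregated CA-BSIs per 1,000 line-days over 3-month periods. This figure will also be used in the cost-effectiveness analysis". The contrast that the economic analysis addresses is given as "the differences in outcome and total costs between the pre-intervention and the post-intervention period". The ratio is then defined: "The ICER is calculated as the incremental costs per case of CA-BSI per 1,000 line-days avoided". A sensitivity analysis on the assumptions made is planned.

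The same Statistical analysis section determines the intervention effect by segmented loglinear regression. It includes slopes because this "corrects for unassociated background trends".

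**The concern.** Two things do not fit together.

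**Units.** A total cost grows with the length of the period and the number of catheters in use. A rate per 1,000 line-days has already been divided by that volume. Several of the costs counted (theme week, manual, timers, reminders) are hospital-level outlays with no natural unit per patient or per line-day. Read literally, the ratio would be larger in a bigger hospital with the same value for money.

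**Contrast.** The effect estimate is built to separate the bundle from background change. The ratio is described as using the aggregated rate and its difference between the two periods, and nothing links it to the model estimate. A decline already under way would be credited to the bundle.

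Objective 4 asks about cost-effectiveness, and the Background section sets it beside excess costs per affected child (about €12,000 in a Belgian neonatal unit, $33,000 in a US pediatric unit). A reader will want to compare the ratio with those figures, and with the trial's own effect estimate.

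**Working it through.** The article states no ICER, cost or line-day figure, so there is nothing to reproduce. The check covers units and trend.

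**Inputs from the article:** 69 children with CA-BSI at baseline, treated here as 69 cases in one year; rates of 11.2 (neonatal) and 7.9 (pediatric intensive care) per 1,000 line-days; periods of 1.9 years and a target rate ratio of 0.70 (Sample size); a 48-month timeline; about €12,000 per CA-BSI (Background).

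**Assumptions:** all 69 cases arose at a rate between 7.9 and 11.2; €100,000 net extra cost, for illustration only; the trend values in step 4.

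1. **Line-days.** 69/11.2 × 1,000 = 6,161 a year and 69/7.9 × 1,000 = 8,734 a year. Over 1.9 years this gives 11,705 to 16,595.

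2. **Conversion factor.** Let ΔC be the total-cost difference, ΔR the rate difference per 1,000 line-days and L the line-days per period, equal in both. Cases averted = ΔR × L/1,000, so ΔC/ΔR = (cost per case averted) × L/1,000.
   - Cases averted: 69 × 1.9 × 0.30 = 39.3. Cost per case averted: 100,000/39.33 = €2,543.
   - Literal ratio at rate 11.2: 100,000/(0.30 × 11.2) = €29,762, a factor of 11.7.
   - Literal ratio at rate 7.9: 100,000/(0.30 × 7.9) = €42,194, a factor of 16.6.
   - With the 141 cases assumed under Sample size, the factor is 141/11.2 = 12.6 to 141/7.9 = 17.8.

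3. **Unequal line-days.** Count infection costs only, at €12,000 per case, with a pre-period rate of 11.2 and a rate ratio of 0.70. Post-period line-days are g times pre-period line-days. The pre-period cost is 131.1 × 12,000 = €1,573,200. The post-period cost is that × 0.70 × g. ΔR = 3.36. Negative values are savings.
   - g = 0.8: ΔC = −692,208; literal ratio −206,014; divided by 11.705, −17,600.
   - g = 1.0: ΔC = −471,960; literal ratio −140,464; divided by 11.705, −12,000.
   - g = 1.2: ΔC = −251,712; literal ratio −74,914; divided by 11.705, −6,400.
   - With costs per 1,000 line-days the ratio is −40,320/3.36 = −12,000 for every g.

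   Rescaling by pre-period line-days therefore recovers the cost per case only when the volumes are equal.

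4. **Trend.** Two 1.9-year periods at either end of 48 months have midpoints 4.0 − 1.9 = 2.1 years apart, or 8.4 quarters, bracketed here by 8 and 9. With no intervention effect and a constant quarterly decline q, the pre/post rate ratio is (1 − q) to the power 8 or 9.
   - q = 2%: 0.85 or 0.83.
   - q = 3%: 0.78 or 0.76.
   - Decline that alone gives 0.70: 1 − 0.70^(1/8) = 4.4%, or 1 − 0.70^(1/9) = 3.9%.

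5. **Price of the model-based effect.** Extrapolating a pre-period slope fitted to 131 cases by 2.1 years gives a log counterfactual variance of about (1/131) × (1 + 2.1²/(1.9²/12)) = 0.120. The post-period count adds 1/91.8 = 0.011. The SE is about 0.36, so a rate ratio of 0.70 has a 95% interval of roughly 0.34 to 1.42.

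**The case against.** The best defence is that total costs means the sum of components, not a hospital-wide sum over a period. In "regarding both the total costs and the number of CA-BSIs per 1,000 line-days" the denominator can be read as governing both terms. If costs are per 1,000 line-days, line-days cancel and the ratio is already euro per CA-BSI averted. A cost denominator is also a detail that a condensed article may leave to the full protocol. This stands in part. The reading is possible but not stated, and the admission-to-discharge horizon suggests, if anything, costs per patient, which would not match the effect term either.

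A reader might infer that the plan commits a definite arithmetic error with a 12- to 17-fold bias. The article does not support that. The multiplier is a conversion factor resting on assumed line-days, and line-days are collected, so with similar volumes the cost per case can be recovered. Only unequal volumes distort it. They are plausible, because the bundle asks daily whether the catheter is still needed.

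A reader might also infer that the plan itself rejects a pre/post contrast as confounded. It does not. It says that slopes correct for background trends, and Sample size openly uses a comparison of levels as a simplification. That the ICER's contrast is unadjusted is also an inference, though a natural one from the reference to the aggregated figure.

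Finally, a model-based effect is not plainly better as the base case. By step 5 its interval would include no effect. If only the averted cases came from the model, savings due to a background decline would remain in the costs.

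**Conclusion.** The point holds as a defect of definition. Followed literally, the ICER is not a cost per CA-BSI averted unless costs share the denominator of the effect. It scales with catheter volume, by about 12 to 17 if 69 cases a year arose at 7.9 to 11.2 per 1,000 line-days over 1.9 years. It also moves with any change in line-days: in the illustration, 20% fewer or more line-days shifts a true saving of €12,000 per case to €17,600 or €6,400, even after rescaling by pre-period volume.

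The ICER's effect term also lacks the trend correction given to the effect estimate in the same section. How much that matters depends on a trend the article does not report. About 4% per quarter would be enough to mimic the whole target effect.

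Severity is minor to moderate. Cost-effectiveness is to be explored as a secondary outcome, a sensitivity analysis is already planned, and the primary result is unaffected.

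**What to change.** - State one basis for both terms: incremental cost per 1,000 line-days divided by CA-BSIs averted per 1,000 line-days, reported as euro per CA-BSI averted. Say over which line-days the one-off implementation costs are spread.
- State that the base-case effect is the pre/post difference in the aggregated rate. Add to the planned sensitivity analysis a version in which both the averted cases and the CA-BSI-related costs come from the segmented model's counterfactual (pre-intervention trend carried forward). State in advance that its interval will be wide and may include no effect.

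This changes only the analysis wording. Line-days, cases and costs are already to be collected. The cost is one further analysis, with an imprecise result that has to be reported as such.
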